**CHAPTER 3**

**STUDY HYPOTHESES**

1. *H. pylori* eradication improves L-dopa ‘onset’ time and prolongs the L-dopa ‘on-time’ duration.
2. PD patients with *H. pylori* infection show clinical improvement in motor disability after eradication therapy of H. *pylori*, assessed using UPDRS-III / PDQ39 questionnaires.

**CHAPTER 4**

**METHODOLOGY**

4.1 Study design and study population.

This is a prospective study which, will be conducted at UKMMC between the months of June 2012 to February 2013. The study population consists of Parkinson’s disease patients on levodopa therapy, who will be consecutively recruited from the neurology outpatient clinic UKMMC. The study will be done after the approval of the *Research Ethics Committee UKMMC*. Patients who fulfill the inclusion and exclusion criteria will be counseled and upon giving informed consent, will be enrolled into the study. Individuals with poor command in English or Bahasa Malaysia will be given explanation with an assistance of an interpreter.

4.2 Patient selection

All known PD patients will be recruited from PPUKM neurology clinic consecutively. They will be assessed for stages and severity of their disease using UPDRS and PDQ39 questionnaires. The following information also will be taken from history: duration of disease, types of treatment and its durations of use, previous use of Proton Pump Inhibitors (PPIs)/H2-antagonist and previous endoscopy, symptoms of gastritis/PUD, other co-morbidities and family histories of Parkinson’s and H pylori infection.

Patients who fulfill the following inclusion criteria will be recruited.

Inclusion Criteria

1. Diagnosis of idiopathic Parkinson’s disease (PD) by a neurologist
2. Age more than 18 years
3. Written informed consent given either by the patient or next of kin
4. Patients on L-DOPA therapy

Exclusion Criteria

1. Patients with a diagnosis of secondary parkinsonism, and Parkinson’s plus syndrome

2. History of recent proton pump inhibitors (PPIs) or Histamine (H2) antagonist use for at least 4 weeks prior to the urea breath test

3. History of recent antibiotics use (less than 6 months)

4. Inability to perform urea breath test

4.3 Study Flow Chart

*For subject who is on proton pump inhibitor, if there is no contraindication will be withhold for 4 weeks and given a later date for Urea Breath Test

Sample recruitment

Assessment for eligibility

(Fulfillment of Inclusion criteria)

Informed consent

Patient assessment (L-dopa ‘onset’ time and ‘on-time’ duration, UPDRS-III & PDQ39) and data collection

Positive urea breath test (UBT)

Eradication therapy of H.pylori (oral esomeprazole 40mg od, oral clarithromycin 500mg bd and oral amoxicillin 1000mg bd x 14/7)

Assessment of clinical response to L-Dopa (L-dopa ‘onset’ time and ‘on-time’ duration) & clinical motor improvement using UPDRS-III and PDQ-39 Questionnaire

3/12 later

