4.5 Study protocol and study tools

Upon consent, patients will be enquired regarding their background and the data will be recorded (Appendix III). Information regarding sociodemographic characteristics (smoking history, alcohol consumption and coffee consumption), previous antibiotics use, concomitant medical conditions, current medications and any gastrointestinal symptoms will be recorded. Height and weight are measured and recorded into the data collection sheet. The clinical response to L-dopa will be documented (looking at L-dopa ‘onset’ time (minutes) and L-dopa ‘on-time’ duration (minutes)). The severity of their Parkinson’s disease will be assessed using PDQ-39 questionnaires and the Unified Parkinson’s Disease Rating Scale (UPDRS)-III.

PDQ-39 (Appendix IV)

PDQ-39 is the most widely used disease-specific patient completed rating scale in PD. It consists of 39 questions covering eight aspects of quality of life: mobility, activities of daily living (ADL), emotional well being, social stigma, social support, cognition, communications and bodily discomfort. PDQ-39 has been tested for reliability and validity51. The maximum total score for PDQ-39 is 156 points signifying a poorer quality of life, with subdivisions for mobility (40), ADL (24), emotional well being (24), social stigma (16), social support (12), cognitive impairment (16), communication (12) and bodily discomfort (12).

The Unified Parkinson’s Disease Rating Scale (UPDRS) (Appendix V)

The UPDRS is a rating scale used to assess the severity of PD. It is useful for clinicians as well as researchers to evaluate the progression of the disease and response to treatment. It is comprised of 4 parts. Part I – Mentation, behaviour and mood, Part II – self evaluation of ADLs, Part III – clinician scored motor evaluation and Part IV – Complications of therapy. The first 3 sections (I to III) are rated with a 5-point scale (0 signifying no disability and 4 signifying maximum disability) while the fourth section is used to evaluate patients with more advanced stage who are on treatment. The maximum score for each section is 16, 52, 108 and 23, respectively, giving a total of 199, being the higher the score the greater the disability from PD.

Urea Breath test protocol (Appendix VI)

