Each subject undergoes UBT to diagnose H. pylori infection. UBT is selected as the most appropriate tool for diagnosing *H. pylori* in this study because it is noninvasive, non-radiotoxic and readily available compared to OGDS. Serology testing is cheaper and widely accessible and has been used in many researches locally and internationally. Unfortunately, serology testing has a specificity of 79-90% and sensitivity of 76-84%38, 52. Furthermore, patients who are positive for *H. pylori* will remain seropositive for as long as 4 years after its eradication even when UBT has long been negative53.

Subjects who are on PPIs or H2 blockers will be given a later appointment for UBT after 4 weeks of stopping these medications. Each patient will be given 75 mg of IRIS 13C urea mixed in Tang™ Orange juice. Breath sample will be taken at 0 minutes, 10 minutes, 20 minutes and 30 minutes. At each breath, subjects will be asked to inhale deeply and hold for 5 seconds and then blow slowly into a bag until its fully inflated. The breath samples collected will be then analysed using the Non-Dispersive Isotope-Selective InfraRed Spectrometer (NDRIS)[IRIS]. Interpretation of the results are based on the IRIS Software 2.3 for analysis of Delta (δ) over baseline (DOB) (Appendix VII).

Delta over baseline (DOB) APPENDIX VII

Delta (δ) over baseline (DOB) of 13C-urea breath test has been shown to correlate with H. pylori severity infection. It correlates significantly with total urease activity in the stomach and hence a quantitative indicator of *H. pylori* load54, 55. DOB also has been studied extensively and the value shown to be correlated with bacterial strain virulence56, intensity of dyspeptic symptom57 and therapy efficacy58. There is no standard acceptable cutoff for DOB value to divide severity into stages yet. This is because there are many companies with different 13C-UBT protocols with differing 13C-urea dosages and timing of breath collections.

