Appendix II

DATA COLLECTION FORM

Subject Initials: Subject #: Date of Visit:

DD MM YR

Paste sticker here Contact Number

A. Checklist:

Parkinson’s Group Control Group

Inclusion Criteria Yes No

1. Diagnosis of idiopathic Parkinson’s disease (PD) by a

neurologist (Hoehn and Yahr Stage I-IV)  

1. Age > 18 and < 90 years old  
2. Written informed consent given either by the patient

or next of kin  

1. Patient on levodopa at least > 1 month  

Exclusion Criteria

1. Patients with a diagnosis of secondary parkinsonism, and

Parkinson’s plus syndrome.  

1. History of recent proton pump inhibitors (PPIs) or histamine (H2)

antagonist use for at least 4 weeks prior to the urea breath test  

1. History of recent antibiotics use (less than 6 months)  
2. Inability to perform Urea Breath Test  

Consent  

|  |
| --- |

UBT date

**Urea Breath Test Result positive**  **negative**

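### The baseline levodopa response is not tied to the acid-suppressant washout: only the breath test is deferred, follow-up status is neither set nor recorded, and the eligibility texts on PPI/H2 users do not agree

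*Protocol*

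**What the plan says.** **Order of assessments.** The flow chart in 4.3 goes from consent to "Patient assessment (L-dopa ‘onset’ time and ‘on-time’ duration, UPDRS-III & PDQ39) and data collection", and only then to the positive UBT, eradication therapy and reassessment at 3 months. Section 4.5 is consistent with this: "Upon consent, patients will be enquired regarding their background and the data will be recorded", and the same paragraph continues "The clinical response to L-dopa will be documented" and then names PDQ-39 and UPDRS-III.

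**Acid-suppressant users.** Three rules apply.
- 4.2, exclusion 2 (repeated in the Appendix II checklist): "History of recent proton pump inhibitors (PPIs) or Histamine (H2) antagonist use for at least 4 weeks prior to the urea breath test".
- 4.3, flow-chart note, for PPI users only: the drug, "if there is no contraindication will be withhold for 4 weeks and given a later date for Urea Breath Test".
- 4.5, UBT protocol: "Subjects who are on PPIs or H2 blockers will be given a later appointment for UBT after 4 weeks of stopping these medications".

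**Follow-up.** Section 4.5 repeats the levodopa, UPDRS-III and PDQ-39 assessments 3 months after eradication therapy. It does not say whether a withheld drug has been resumed by then, and asks for no medication record at that visit.

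**Checklist.** Appendix II adds limits that are not in 4.2: "neurologist (Hoehn and Yahr Stage I-IV" as part of the diagnosis item, an upper age limit of 90, and "Patient on levodopa at least > 1 month".

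**The concern.** This is a single-group before-after study, so no control arm absorbs a change in co-medication between the two primary measurements. The protocol's own rationale (1.3) is gastroduodenal: it attributes a poor levodopa response to delayed gastric transit and impaired duodenal absorption. A change in a gastric drug between baseline and follow-up, in some patients only, would compete directly with the hypothesis under test.

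A second effect follows from the deferral. The deferred patient's baseline is older when treatment starts, which leaves more time for disease progression or changes in levodopa dosing to enter the contrast.

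The eligibility wording adds to this. Whether a current or recent user enters, and in what state, depends on which page the site follows.

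**Working it through.** The protocol states no figure on this point, so the check is mainly a comparison of texts.

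**1. What is deferred.** 4.3 and 4.5 give users a later date for the UBT. No sentence moves or repeats the levodopa, UPDRS-III or PDQ-39 baseline. A site that follows the listed order may assess a user at consent, while still on the drug.

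**2. Interval between the two assessments.** Assume prompt UBT and treatment, 3 months counted as 13 weeks, and counting from the end of the 14-day course.
- Not deferred: 2 + 13 = 15 weeks.
- Deferred: at least 4 + 2 + 13 = 19 weeks, which is 4/15 = 27% longer.

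**3. Acid-suppressant status of a deferred patient at baseline and at month 3.** The middle column assumes that the consent-visit baseline is taken before the drug is stopped.

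| | Baseline at consent, still on drug | Baseline at UBT visit, after washout |
|---|---|---|
| Drug resumed by month 3 | on / on: matched | off / on: differs |
| Drug not resumed | on / off: differs | off / off: matched |

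The protocol does not say which row applies. Moving the baseline equalises the interval and gives every patient the same starting state, but does not by itself guarantee a match at month 3. Status must also be recorded at both visits.

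**4. Size.** If a share p of analysed patients changes status and the change shifts onset time by d minutes, the mean before-after change moves by p × d. The protocol gives neither p nor d. Purely as an assumed range, p from 10% to 30% and d from 5 to 20 minutes gives:
- low end: 0.10 × 5 = 0.5 minutes;
- high end: 0.30 × 20 = 6.0 minutes.

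The result is zero if status matches. For scale, 4.4 plans on 58 minutes after a 25% improvement. Read as a share of baseline, this gives 58/0.75 = 77.3 and a difference of 19.3 minutes. The assumed range then runs from 2.6% to 31% of the planned effect, which is too wide to serve as evidence, and its direction is unknown.

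**5. Exclusion 2, read literally.**
- A patient whose two-week course ended the day before the UBT did not use the drug for 4 weeks, so is not excluded. If the course was already over at enrolment, the deferral rules, which address patients who are on the drug, do not catch this patient either.
- A long-term user who has stopped for 4 weeks is eligible under 4.5, yet can be ticked out on the checklist's plain yes/no item.

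The UBT reading rule (4.5, Appendix X) still provides for PPI, H2 or antibiotic use in the last 4 to 6 weeks, so the protocol expects such exposure. That rule settles only values between 2.5 and 4.0.

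**6. Checklist against 4.2.** 4.2 has age above 18 and levodopa therapy, with no upper age, stage or minimum duration. Appendix II has all three. A patient aged 92, in stage 5, or in the first month of levodopa passes one list and fails the other.

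**The case against.** Much of the opposing case limits how far the point goes.

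- **Before and after differ in acid suppression.** A reader might infer this as fact. The documents do not support it: they are silent on whether the drug is resumed, and if it is, a patient assessed on the drug at consent is matched at month 3.
- **4.2 flatly contradicts 4.5.** This is also tempting. But exclusion 2 is timed to the UBT, and a user who stops for 4 weeks can meet it by that date. The two can be read as one loosely worded washout. The fault is ambiguity, and the 4.3 note, which omits H2 blockers, adds to it.
- **The baseline is taken on the drug.** The protocol permits this but does not state it. No text says when withholding starts relative to the assessment. The flow chart is available here only as running text, so the box to which its note attaches cannot be seen. The wording of 4.5 nevertheless supports the order.
- **Exposure is already recorded.** This holds for baseline: 4.2 takes a history of PPI/H2 use and 4.5 records current medications. It does not hold for follow-up.
- **The checklist mismatch is a separate matter.** Correct. It is a plain inconsistency and lends no weight to the confounding argument.

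What stands is that the text allows mismatched baselines and contains nothing to prevent or detect them.

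**Conclusion.** The point holds as a gap in design and consistency. As written, a deferred patient's primary-endpoint baseline can be taken on acid suppression and at least 4 weeks earlier relative to treatment than in other patients, and status at 3 months is uncontrolled and unrecorded. The confounding is possible, limited to deferred UBT-positive patients, and of unknown size and direction; no percentage of the planned effect should be attached to it. This rests on taking the listed order in 4.3 and the consent-visit wording in 4.5 at face value. The ambiguous exclusion 2 and the three extra checklist limits rest on no assumption, since they can be read directly from the text. The correction is cheap and worth making, but the point alone does not invalidate the study.

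**What to change.** 1. Take the baseline levodopa response, UPDRS-III and PDQ-39 at the UBT visit, before the result is known. Hand out the 72-hour diary (Appendix III) beforehand so that it is complete by that visit.
2. Record PPI and H2-blocker use at that baseline and again at 3 months.
3. Add a sensitivity analysis excluding patients whose acid-suppressant status differs between the two assessments. This is needed because item 1 alone would create a mismatch in anyone who has resumed the drug by month 3.
4. Reconcile 4.2, 4.3, 4.5 and Appendix II on PPI/H2 users: say whether deferred users are eligible, whether H2 blockers fall under the 4.3 note, and whether exclusion 2 means a duration of use or a window before the UBT. The choice of clinical rule is for the investigators.
5. Make the 4.2 criteria and the Appendix II checklist identical on stage, age and levodopa duration.

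The cost is one re-ordered box, an earlier diary hand-out, one extra medication record at follow-up, and wording changes. The sensitivity analysis loses precision. On the 4.4 figures, 50 recruited less 10% leaves 45, so the calculated 39 is kept only if no more than 6 patients are set aside. It should be reported as supportive.

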4.4 Sample size calculation

The sample size iscalculated based on the following formula:

n = 2(sd)2 1 + (r-1)ρ2 _ Pρ2

f(α,β)

diff2 r 1 + (P-1)ρ

= 2 (sd)2

1 – ρ2

f(α,β)

diff2

Note: P = No. of measure before test

r = No. of measure with test

ρ = Correlation between pairs of measurement before and after eradication therapy of *H. pylori*

Ref: Phillips R., Campbell M (1997) Journal Pharmaceutical Statistic 7(2) 215-225

Based on study by Lee WY *et al* in 2008, comparing clinical response to L-dopa before and after *H.pylori* eradication therapy in *H.Pylori* infected PD group, the mean L-dopa ‘onset’ time after *H.Pylori* eradication is 58 minutes (25% improvement from baseline). The calculated number of patients needed in this study is 39 patients. Given the possibility of 10% drop out, a total of 50 patients will be recruited. The power of the study is set at 95% with level of significance of 5%. We will screen a total of 120 patients who were diagnosed Parkinson’s disease using Urea Breath Test (UBT) in order to give us 43 patients with positive UBT. Recruitment of total 50 Parkinson’s patients with H. *pylori* infection positive in this study gives a power of study of 95%.

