**Study Objectives**

Primary Objectives:

- To compare the clinical response to L-dopa before and after *H. pylori* eradication therapy in the *H. pylori* infected PD group. (L-dopa ‘onset’ time (minutes) and L-dopa ‘on-time’ duration (minutes) ).

Secondary Objectives:

- To assess clinical motor improvement before and after *H. pylori* eradication therapy in infected PD group, using the UPDRS-III and PDQ39 questionnaires.

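### Section 4.4 sizes a one-group before-after comparison with a two-group formula, so 39 patients and 95% power do not belong together

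*Protocol*

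**What the plan says.** The primary objective in Chapter 2 of the protocol is "To compare the clinical response to L-dopa before and after" eradication therapy, within the infected Parkinson's disease group. The flow chart (4.3) and the treatment and follow-up text (4.5) describe one path: every patient with a positive breath test is treated and reassessed three months later. No comparator appears in the objectives, the hypotheses, the flow chart or the follow-up text.

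Section 4.4 gives the formula "n = 2(sd)2 1 + (r-1)ρ2 _ Pρ2" (the text extraction has broken its layout) and then its reduced form, with the factor 1−ρ². The note beneath defines "P = No. of measure before test", "r = No. of measure with test" and ρ as "Correlation between pairs of measurement before and after eradication therapy of" *H. pylori*. It does not define sd and gives no value for sd, ρ or diff.

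The effect comes from a cited study in which mean L-dopa onset time after "eradication is 58 minutes (25% improvement from baseline". The result is stated as "The calculated number of patients needed in this study is 39 patients". On power, the section says: "The power of the study is set at 95% with level of significance of 5" per cent. It does not say whether the test is one- or two-sided.

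**The concern.** Two features of the reduced formula do not fit the design. The factor 1−ρ² is the share of follow-up variance left after regression on baseline, as in an analysis of covariance. The leading 2 arises when two independent group means are subtracted. Together they give the size of each arm in a parallel-group comparison. A before-after comparison in one group depends instead on the variance of each patient's change, where ρ enters as 1−ρ.

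This formula is the only justification offered for the sample size, and so for how many patients receive the 14-day course. If it belongs to another design, the 95% power put before the ethics committee is not the power of this study. Because the inputs are not printed, nobody outside the study team can tell how far off it is.

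**Working it through.** **1. Reduced formula.** With P = r = 1, the term multiplied by r−1 vanishes and the denominator 1+(P−1)ρ equals 1. The bracket becomes 1−ρ², as the protocol prints:

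n(printed) = 2·sd²·(1−ρ²)·f/diff², with f = (z_α + z_β)².

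**2. Can 39 be reproduced?** No, because sd and ρ are missing. One can only ask what they would have to be:
- Two-sided 5% and 95% power: f = (1.960 + 1.645)² ≈ 12.995. One-sided: f ≈ 10.822.
- If 58 minutes is 75% of baseline, baseline is 58/0.75 = 77.3 and diff is 19.3 minutes. If 25% is taken of 58, diff is 14.5 minutes.
- Solving 39 = 2·sd²·(1−ρ²)·f/diff² gives sd·√(1−ρ²) = diff·√(39/(2f)). Two-sided with diff 19.3, this is 19.33·√(39/25.99) = 23.7 minutes.
- The other combinations give 17.8 (two-sided, 14.5), 26.0 (one-sided, 19.3) and 19.5 (one-sided, 14.5).

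**3. Formula for this design.** Let sd be the standard deviation on a single occasion, equal before and after. The variance of the change is sd² + sd² − 2ρ·sd² = 2·sd²·(1−ρ), so

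n(paired) = 2·sd²·(1−ρ)·f/diff².

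**4. Ratio.** n(printed)/n(paired) = (1−ρ²)/(1−ρ) = 1+ρ. The sd, diff and f cancel, so the gaps in step 2 do not affect the ratio.

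**5. Consequences if 39 came from the printed formula.** The paired requirement is 39/(1+ρ). The standardised effect with 39 completers is √((1+ρ)·f), so two-sided power by the normal approximation is Φ(√((1+ρ)·12.995) − 1.960). At ρ = 0.5 this is Φ(√19.49 − 1.960) = Φ(2.455) = 99.3%.

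| assumed ρ | paired n, normal | paired n, t | power at 39, normal | power at 39, t |
|---|---|---|---|---|
| 0 | 39 | 41 | 95.0% | 94.0% |
| 0.3 | 30 | 32 | 98.4% | 98.0% |
| 0.5 | 26 | 29 | 99.3% | 99.0% |
| 0.7 | 23 | 25 | 99.7% | 99.6% |

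The two-sided results are the same for either reading of diff. With a one-sided test, power at 39 (t) is 97.9%, 99.0% and 99.5% at ρ = 0.3, 0.5 and 0.7. The two formulas agree only at ρ = 0. A negative ρ would reverse the direction: at ρ = −0.3 the paired n is 56, and power at 39 is about 84% to 85%.

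**The case against.** The strongest reply is that the error is on the safe side. Two measurements of one patient are normally positively correlated, and for any positive ρ the printed formula asks for more patients than a paired test needs. This stands, and it limits the severity. The excess over the assumed range is 39−30 = 9 to 39−23 = 16 patients, or 7 to 14 with the t distribution. It is not even shown to be surplus: the primary objective names both onset time and on-time duration, while 39 is justified on onset time alone.

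A second reply is that sd is undefined, so the ratio 1+ρ is itself conditional. That is correct. If sd were already the standard deviation of the change, the ratio would be 2·(1−ρ²) instead. The single-occasion reading is the natural one, because a standard deviation of change already contains ρ and needs no further ρ term. Under either reading the printed formula is not the paired one.

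Two stronger readings are tempting, and the documents support neither:
- A reader might infer that 39 is a per-group number and that the trial is therefore badly underpowered. The only trace of a second group is a Control Group tick box on the data collection form (Appendix II). No objective, hypothesis or flow-chart step uses one.
- A reader might infer that the inflated formula has put the target out of reach. Section 4.4 expects 43 positive tests from 120 screened, and 43 less 10% is 38.7, about 39. The gap between 43 and the 50 to be recruited is a separate inconsistency that this formula does not cause.

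**Conclusion.** The point holds as a mismatch between formula and design, with unreported inputs. It is not a demonstrated slip of arithmetic. That the formula belongs to a two-group comparison follows from the protocol's own text and from algebra. The factor 1+ρ also assumes a single-occasion sd that is equal before and after. The patient numbers and powers further assume that 39 came from the printed formula and that ρ lies between 0.3 and 0.7. The minute values are only illustrations, because neither diff nor sidedness is stated.

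On those assumptions the study has more power for onset time than the protocol claims, and the primary comparison is not put at risk by this error. What is wrong is the statement that 39 patients correspond to 95% power. The point is moderate.

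**What to change.** In section 4.4, replace the formula with n = 2·sd²·(1−ρ)·f/diff², or equivalently n = sd_change²·f/diff². Define sd. Print the values actually used for sd (or the standard deviation of change), ρ and diff, with their source, and say whether the test is one- or two-sided.

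Then either restate the required number, or keep the present target and state the power it gives over a range of ρ. The section repeats 95% power for the 50 patients to be recruited, so that sentence should be revised at the same time.

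The cost is one recalculation and one rewritten paragraph. For any ρ of zero or more, and with sd a single-occasion value, no extra patients are needed, apart from about two at ρ = 0 if the t distribution is used (41 against 39).

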**1.2 *Helicobacter pylori***

*Helicobacter pylori* is a spiral-shaped, gram-negative bacillus that inhabits the gastric mucosa. It is one of the most common infections found in humans worldwide. It was first discovered by Warren and Marshall in 1982 and was then called *Campylobacter pylori*. By the end of the 1980s there was a recognised association between *H. pylori* and antral gastritis and by early-to-mid 1990s further research showed evidence of a link between chronic *H. pylori* infection and gastric malignancies.

The prevalence of *H. pylori* infection varies worldwide ranging between 20-80%15. This variation of prevalence is due to several factors such as age, socioeconomic status and ethnicity. In their review, Pounder and Ng16 identified two major patterns of *H. pylori* infection prevalence. The first group showed a high prevalence of *H. pylori* infection before the age of 10 which remained high across all age groups (Appendix II). The second group had a low childhood prevalence which increased with age which occurred in developed countries.

In Malaysia, an overall prevalence of 26-60% was noted. Goh et al17 studied the prevalence of *H. pylori* infection in patients undergoing endoscopy in the University Hospital in Kuala Lumpur between 1994-1995. They found that the Indian race had the highest prevalence of *H. pylori* than either Chinese or Malays with seropositivity of 61.8%, 48.5% and 16.4% respectively. A study done by Gurjeet et al18 among endoscoped patients in north eastern Peninsular Malaysia in 2003 found a low prevalence of 13.5%. They also found similar differences in racial distribution of prevalence for Malays (6.6%), Chinese (24.1%) and Indians (28.6%). Another study by Uyub19 looking at 5,370 healthy blood donors in Northern Peninsula showed a lower prevalence of 14.2%.

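### Section 4.4: the recruitment target of 50 follows neither from 39 patients with 10% drop-out nor from the 43 positives expected from 120 screens

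*Protocol*

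**What the plan says.** All the figures stand in one paragraph of the protocol, section 4.4 (Sample size calculation), in this order:

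- The size from the formula: "The calculated number of patients needed in this study is 39 patients".
- The recruitment target: "Given the possibility of 10% drop out, a total of 50 patients will be recruited".
- The design settings: "The power of the study is set at 95% with level of significance of 5" per cent.
- The screening number: "We will screen a total of 120 patients who were diagnosed Parkinson’s disease using Urea Breath Test (UBT"), and its purpose: "in order to give us 43 patients with positive UBT".
- The closing claim about recruiting 50 patients: "infection positive in this study gives a power of study of 95" per cent.

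The 43 and the 50 count the same people. The closing sentence describes the 50 as Parkinson's patients with *H. pylori* infection. The flow chart in 4.3 and the treatment and follow-up paragraphs in 4.5 show that only breath-test-positive patients receive eradication therapy and return at three months.

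The positivity rate behind the screening number is not stated. Section 1.2 offers background only: "In Malaysia, an overall prevalence of 26-60% was noted".

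**The concern.** A reader cannot tell from 4.4 how many infected patients the trial sets out to enrol. The drop-out sentence gives 50 and attributes it to 10% loss alone, which does not produce 50 from 39. The screening sentence is built to deliver 43. The power sentence returns to 50 with the same 95% that was the setting for the calculation that gave 39.

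The enrolment target, screening number and power are what an ethics committee approves and what a final report is read against. If the 120 screens go exactly as expected, the trial ends with 43 treated patients. By one sentence it has what it planned for; by two others it is seven short. The paragraph gives no basis for choosing between these readings.

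**Working it through.** **Inputs, all from protocol 4.4:** 39 patients calculated; 10% drop-out; 50 to be recruited; 120 screened; 43 positives expected; power 95%; significance level 5%. Sidedness is not stated, so both cases are shown.

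**Step 1. Try to reproduce the 50.**
- n/(1 − d) = 39/0.90 = 43.3, rounded up to 44.
- n × (1 + d) = 39 × 1.10 = 42.9, rounded up to 43.

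Neither convention gives 50. The second gives exactly the 43 of the screening sentence. Solving for the loss that would give 50: 1 − 39/50 = 22% by the first convention, and 50/39 − 1 = 28% by the second.

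**Step 2. Compare the screening number with the target.**
- Implied positivity: 43/120 = 35.8%.
- Screens expected to yield 50 positives: 50/0.3583 = 139.5, so about 140.
- Shortfall at 120 screens: 50 − 43 = 7 patients.
- With X ~ Binomial(120, 43/120), P(X ≥ 50) = 0.109, about 11%.

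**Step 3. Power for each number, taking 39 analysed as 95%.** Anchoring on 39 removes the need for an SD or a correlation. By the normal approximation,

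power(n) = Φ( (z_α + z_0.95) × √(n/39) − z_α )

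Two-sided, z_α + z_0.95 = 1.960 + 1.645 = 3.605. For n = 45: 3.605 × √(45/39) = 3.872; 3.872 − 1.960 = 1.912; Φ(1.912) = 97.2%.

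| Situation | Analysed | Power, two-sided | Power, one-sided |
| --- | --- | --- | --- |
| 43 recruited, 10% lost | 38.7 | 94.9% | 94.9% |
| Calculated size | 39 | 95.0% | 95.0% |
| 50 recruited, 10% lost | 45 | 97.2% | 97.1% |
| 50 recruited, none lost | 50 | 98.3% | 98.1% |

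So 50 recruited corresponds to 95% power only if about 11 patients (22%) are lost. At the stated 10% loss, the 95% is an understatement.

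**Step 4. Which figure is out of line?** The sequence 39 → 43 → 120 screens holds together: 43 less 10% is 38.7, within one patient of 39. The 50 fits neither the step before it nor the step after it.

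**The case against.** The best defence is that most of the paragraph works. The 39 is a number to be analysed, not an enrolment figure, and 43 is 39 plus a tenth, a common shortcut. The 120 screens are sized to match. Power of 95% is a design setting, and the last sentence can be read as saying that recruiting 50 secures it after losses. Recruiting more than the number to be analysed is ordinary practice, and here it errs on the safe side. All of this stands. It places the fault in one figure and limits its consequence, but it does not explain the 50. The text gives 10% drop-out as the only reason for it, and the screening plan does not provide for it.

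A reader might infer stronger conclusions, which the protocol does not support:

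- *That the trial is underpowered.* On its own figures it is not: 43 recruited with 10% loss keeps about 94.9%.
- *That 50 cannot be reached.* It is not expected, but a chance of about 11% is not an impossibility.
- *That the paragraph claims 95% power outright for both 39 and 50.* Only the 50 is said to give 95%. For 39 the link is indirect, through the power setting and the calculated size.
- *That the prevalence figures in 1.2 show the yield of 43 to be unrealistic.* The implied 35.8% lies within the 26–60% given there. The same section also cites 13.5% and 14.2%, but the Malaysian surveys are of endoscopy patients and blood donors, not Parkinson's patients. In 1.3, 70% of Parkinson's patients in one study were positive, though by serology rather than breath test. These rates do not settle the matter either way.

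**Conclusion.** The point holds as an inconsistency in the stated figures. Fifty is six or seven more than 39 with 10% loss requires, and seven more than the planned screening is expected to supply. It would need 22% loss, or about 97% power at 10% loss, to be justified, and about 140 screens rather than 120 to be expected. The effect on power is small: 0.1 percentage points below 95% if 43 are recruited, and about two points above it if 50 are. Severity is minor to moderate, and the remedy is a restatement of figures.

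This rests on taking 39 as correct for 95% power. That number cannot be reproduced from 4.4, which gives no value for the SD or the correlation. The comparisons above are relative to 39, so they do not depend on those values. The 11% also assumes that each screened patient is positive independently with probability 43/120.

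**What to change.** Replace the paragraph's figures with one chain. Which target to keep is the sponsor's choice.

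- **Simplest, keeping the 120 screens:** 39 evaluable patients; 43 expected breath-test-positive patients at a stated positivity of 35.8%; 10% loss; about 95% power for the roughly 39 analysed. Remove the 50 and the closing sentence that attaches 95% power to it. This costs a rewording and no further screening.
- **If 50 is kept:** state its true basis, either 22% loss for 95% power or about 97% power at 10% loss. State also that it is expected to need about 140 screens, 20 more than planned. That number is sized to the average: at the same positivity, 140 screens reach 50 or more about 54% of the time.

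In either case, state the assumed positivity, and give the power once, for the number to be analysed.
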